### Secondary outcome – return to sport and physical function

According to recommendations made in the systematic review by Witjes and colleagues, we will assess return to sport by validated questionnaires and assessment of physical performance [31]. Patients are asked what kind of sport they perform (and whether this has changed due to the surgery), frequency and when they restarted after TKA. The Tegner rating scale is a validated questionnaire to assess level of sports and will be used in the current study [32–34]. The University of California Los Angeles (UCLA) activity scale is furthermore validated and assessed for cross-cultural adaptation in the Dutch population according to the ISPOR manual (The Professional Society for Health Economics and Outcomes Research) [35, 36]. The UCLA and Tegner scale will be completed preoperative and 1 year postoperative (Table 1).

Secondly, objective physical function before and 1 year after surgery will be assessed using 3 performance based measurements (PBMs) recommended by the Osteoarthritis Research Society International (OARSI): 30 s chair test (30 s-CST), 40 m fast paced walk test (40 m-FPWT), and the stair climb test (SCT) [37]. The PBMs will be done according to a standardized protocol that will be followed in all participating centers.

### Secondary outcome – return to work

All patients of working age (18–67 in the Netherlands) are invited to complete questionnaires 1 year after the index surgery to determine (Table 1):Whether or not patients return to their (original) workHow long after the index surgery they returned to workWorking hours per weekPhysical job demands according to the US Department of Labor’s Dictionary of Occupational Titles (sedentary, light, medium, heavy, and very heavy) [38].

### Secondary outcome – psychological factors

Main psychological factors that are evaluated are pain coping, pain catastrophising and depression. Patients are invited to complete 3 validated questionnaires before surgery, at the 5 and 10 year follow-up mark (Table 1). The Pain Self Efficacy Questionnaire (PSEQ) asks patients to take their pain into account when rating their self-efficacy beliefs [39, 40]. The Patient Health Questionnaire (PHQ-2) is a two-item questionnaire that is an accurate screening tool for major depressive disorders [41, 42]. The Pain Catastrophizing Scale (PCS) explores catastrophic thinking and its influence on pain behaviour [43, 44].

### Statistical analysis

Sample size calculation was aimed at non-inferiority of the Attune knee compared to the LCS knee, the predecessor of the Attune. A non-inferiority margin of 1.5% was assumed. Survival data of the LCS was extracted from a meta-analysis on long-term survivorship studies of the LCS TKA (mobile bearing cemented and uncemented implants) [45]. Pooled 10 year survivorship of the LCS was 98.1% [45]. Based on α = 0.05, power (1-β) of 0.90 and both true proportion (p) and null hypothesis proportion (p0) of 98,1%, a sample size of *n* = 709 was calculated with a one-sided test [46, 47]. Taking drop- outs and death within 10 years into account (approximately 20–25%), we are aiming for inclusion of *n* = 900 knees.

All data will be collected in Research Manager (Cloud9 software, Deventer, Netherlands) and exported for analysis to SPSS Statistics 26.0 (IBM SPSS, New York, USA). Data is coded and the encryption key is stored on the local hospital server of the participating institution. Statistical analysis will be mainly descriptive. Baseline characteristics and results will be described as means with standard deviations (SD) or 95% confidence intervals (95% CI), medians with interquartile ranges (IQR) or frequencies with accompanying proportions. Revision rates will be calculated by use of Kaplan–Meier survival analysis and competing risk analysis, where death is considered a competing risk [48]. Multivariable Cox proportional hazard analyses will be performed to assess the influence of radiolucent lines and implant alignment on implant survival and hazard ratios (HR) with 95% CI will be calculated. Mixed model analysis for repeated measures will be used for assessment of change in PROMs scores during follow-up. Multivariate linear regression analysis will be used to assess the association of radiolucent lines, implant alignment and preoperative psychologic scores (PSEQ, PCS and PHQ-2) with PROMs after 1, 5 and 10 years after index surgery.

Descriptive statistics is provided on the proportion of patients that return to sport, what kind of sports they do (and whether this has changed due to surgery), the frequency and time to restart sports after TKA (in weeks). Improvements in Tegner score, UCLA activity scale and PBMs will be assessed with paired T-tests (or Wilcoxons Ranks sum test in case of non-parametric distribution). Descriptive statistics is provided on the proportion of patients of working age that return to work, time to restart work, working hours per week and physical job demands.

For all analyses, the significance level is set at 5% (*p* < 0.05).

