## Methods/Design

### Study design

The current study is a prospective cohort study. Patients will be recruited from high-volume TKA orthopaedic departments in the following 6 hospitals in the Netherlands:Spaarne Gasthuis, Hoofddorp (3 participating surgeons with extensive experience with uncemented fixation), coördinating siteBergman clinics, Rijswijk (2 participating surgeons with extensive experience with uncemented fixation)Medisch Spectrum Twente, Twente (2 participating surgeons with limited experience with uncemented fixation)Maastricht Universitair Medisch Centrum, Maastricht (2 participating surgeons with limited experience with uncemented fixation)Alrijne Ziekenhuis, Leiderdorp (2 participating surgeons with average experience with uncemented fixation [limited to unicondylar knee arthroplasty])Bravis Ziekenhuis, Bergen op Zoom (1 participating surgeon with extensive experience with uncemented fixation)

All surgeons with limited experience regarding uncemented TKA fixation are extensively trained by experienced colleagues and the implant manufacturer before participation in the study.

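### With 709 evaluable knees, one-sided 5% error and 90% power cannot both hold: the sample-size formula takes the variance at 98.1%, not at the implied boundary of 96.6%

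*Protocol article*

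**What the plan says.** All the inputs stand in the sample-size paragraph of the article's Statistical analysis section.

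- Aim: "Sample size calculation was aimed at non-inferiority of the Attune knee compared to the LCS knee". There is no concurrent control arm; under Study design, "The current study is a prospective cohort study". The comparison is therefore one cohort against a fixed literature value.
- Reference value: "Pooled 10 year survivorship of the LCS was 98.1"%.
- Margin: "A non-inferiority margin of 1.5% was assumed".
- Error rates and proportions: "Based on α = 0.05, power (1-β) of 0.90 and both true proportion (p) and null hypothesis proportion (p0) of 98,1"%.
- Result: "709 was calculated with a one-sided test".
- Allowance for loss: "Taking drop- outs and death within 10 years into account (approximately 20–25"%), after which "we are aiming for inclusion of" 900 knees.

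The boundary that the margin implies, 98.1% − 1.5% = 96.6%, is not printed. The value labelled as the null proportion is 98.1%, the same as the assumed true value. For the endpoint, the section plans Kaplan–Meier and competing-risk analysis. It names no non-inferiority test and no type of confidence bound.

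**The concern.** In a one-sample non-inferiority test, the type I error is defined at the boundary, here 96.6%. The formula behind 709 uses the variance at 98.1% for the error term as well as for the power term. With failure rates of 1.9% and 3.4% those variances differ a great deal, so the nominal error rates need not be the true ones.

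Two things are at stake. If the Attune truly matches its predecessor, the chance of failing to show it may be well above the stated 10%. If a simple bound is used instead to recover power, an implant sitting at the unacceptable 96.6% would pass more often than the stated 5%.

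**Working it through.** **Inputs (from the article):** true survivorship 0.981; margin 0.015; one-sided α 0.05 (z = 1.6449); power 0.90 (z = 1.2816); 900 knees; 20–25% loss over 10 years. Derived boundary: 0.966.

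**1. Reproduce the plan's figure.**
n = p(1−p)·[(z₀.₉₅ + z₀.₉₀)/margin]² = 0.981 × 0.019 × (2.9264/0.015)² = 709.4.
This matches 709. Other routes do not: one-sided 0.025 gives 871, a two-arm design gives 1,419 per arm, and the arcsine formula gives 963.

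**2. Compare the variances.**
At 98.1%: 0.981 × 0.019 = 0.0186. At 96.6%: 0.966 × 0.034 = 0.0328. The ratio is 1.76.

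**3. Put the boundary variance in the error term.**
n = [(1.6449·√(0.966 × 0.034) + 1.2816·√(0.981 × 0.019))/0.015]² = [(0.2981 + 0.1750)/0.015]² ≈ 995.
Power at 709 = Φ[(0.015·√709 − 0.2981)/0.1365] = Φ(0.742) = 77.1%.

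**4. Exact binomial sums at n = 709.** The expected number of revisions is 709 × 0.034 = 24.1 at the boundary and 709 × 0.019 = 13.5 at 98.1%. Size is the probability of meeting the cut-off at a 3.4% failure rate; power is the same probability at 1.9%.

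| Non-inferior if revisions are at most | Corresponding test | True size | Power |
|---|---|---|---|
| 15 | exact binomial | 3.1% | 72.2% |
| 16 | score, or log-log bound | 5.1% | 80.2% |
| 17 | Wald bound | 8.0% | 86.5% |
| 18 | none of these tests | 12.0% | 91.2% |

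The first cut-off to reach 90% power has a size of 12.0%. The last to stay within 5% has a power of 72.2%. The Wald test, which the formula presumes, misses both stated figures.

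**5. Kaplan–Meier analysis, by simulation.** Assumptions: 900 knees, and exponential times to revision and to loss. The revision rate is −ln(0.981)/10 = 0.0019 per year under equality and −ln(0.966)/10 = 0.0035 at the boundary. The loss rate is −ln(0.80)/10 = 0.022 to −ln(0.75)/10 = 0.029 per year. Runs of 4,000 to 20,000 replicates give approximately:

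| One-sided 95% bound at 10 years | Power | Type I error |
|---|---|---|
| log-log | 80–82% | 4.5% |
| plain Greenwood | 87–89% | 7–8% |

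**6. Upper limit on information.** If all 900 knees were followed for 10 years, power would be 85.8% (exact binomial) or 86.7% (normal formula with the boundary variance).

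**The case against.** The best defence has four parts.

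- **The formula is standard and was applied correctly.** This stands. A reader might infer that 709 is a miscalculation, but step 1 shows that it is not. The fault lies in relying on the approximation at failure rates of 2–3%.
- **The article names no test, so no single true power can be asserted.** This also stands. A reader might take 72% as the real power. That figure belongs to an exact binomial test on 709 completers, which the article does not plan and whose size is only 3.1%. The planned Kaplan–Meier analysis does better. The choice of test still does not rescue the statement, because no revision cut-off at 709 delivers the printed pair.
- **Knees lost before 10 years still contribute to a Kaplan–Meier estimate.** True, and the simulation includes them. With error controlled, power remains about 80–82%. Greenwood comes near 90% only by letting the type I error rise to 7–8%.
- **The study is observational, reports survivorship as its objective and describes its analysis as largely descriptive.** This lowers the severity. It does not make the printed error rates correct, and the enrolment target is justified by them alone.

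**Conclusion.** The concern holds with moderate severity. At 709 evaluable knees, one-sided 5% error and 90% power against a 96.6% boundary are not jointly attainable. With error controlled under Kaplan–Meier and a log-log bound, power is about 80–82%. The chance of missing true equality with the predecessor is then about 18–20% rather than 10%.

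The binomial figures rest only on the article's own inputs and on treating 10-year survival as a proportion of fully followed knees. The Kaplan–Meier figures also assume exponential revision and loss times, which the article does not state.

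A reader might also conclude that enrolment must rise: 995 evaluable knees, inflated for 20–25% loss, would be 995/0.80 = 1,244 to 995/0.75 = 1,327. That follows only if 90% power must be kept. Nothing in the article makes the study depend on it, and an honest statement of the lower power is enough.

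**What to change.** Rewrite the sample-size paragraph on three points:

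1. State the hypotheses with the boundary: H0, 10-year survivorship at most 96.6%, against H1, above 96.6%. Describe 98.1% as the reference and assumed true value, not as the null proportion.
2. State the decision rule: non-inferiority is concluded if the one-sided 95% lower log-log Kaplan–Meier bound at 10 years lies above 96.6%. Plain Greenwood or Wald bounds should not be used for this conclusion, because their error is about 7–8%.
3. Restate the power: with 900 knees and 20–25% loss over 10 years, about 80% if true survivorship is 98.1%, with the exponential assumption named. If an exact binomial test on 709 completers is preferred, state about 72%. A score test on the same knees has about 80% power but a true size of 5.1%, so it should not be described as strictly holding 5%.

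The cost is one paragraph and a less favourable stated power. Enrolment, follow-up and data collection do not change.

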Patients are asked to complete questionnaires before surgery and at every follow-up visit, which consists of 6 validated PROMs (Table 1). The EuroQol 5D-5L is a validated questionnaire for general health [23]. The Oxford Knee Score (OKS) is a validated and extensively used 12-item questionnaire for the subjective evaluation of knee function and pain [24, 25]. The Forgotten Joint Score 12 (FJS-12) is a knee specific questionnaire to assess joint awareness during daily living and has less of a ceiling effect when compared to other knee specific PROMs (e.g. patients ‘forget’ about a well-functioning joint) [26, 27]. Patellofemoral pain and function will be assessed with the Kujala Anterior Knee Pain Scale (AKPS) [28–30]. Finally, patients are asked to rate their pain (during activity and rest) and satisfaction concerning the TKA on a Numeric Rating Scale (NRS). All questionnaires are supplemented with 2 anchor questions that measure change in pain and daily function since index surgery.

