There are several challenging aspects in the design of the current study. Minimizing loss to follow-up can prove difficult. Due to the highly successful nature of TKA, patients may not be willing to return for a clinical visit 10 years after surgery. Another deterrent to follow-up may be the high number of outcome measures recorded. Digital options for collection of the primary outcome measures (revision rate, complication rate and PROMs) can provide useful in this aspect and maximize data collection. The multicentre design always introduces bias due to the heterogeneity of surgical environment and hospital-specific factors. This is minimized by standardized surgical procedures and regulations already in place in all orthopaedic clinics (by the Dutch Orthopaedic Society). Nonetheless, a multicentre design also allows for generalisability of results and provides robust external validity for European health care environments. Furthermore, the role of industry funding should be considered as a possible source of bias for our study. However, the current study is investigator-initiated (i.e. protocol was constructed before the industry knew of its existence) and the role of the industry is as a funding body only. Therefore, there was no influence on methodology and there will be no influence on the results or their interpretation.

In conclusion, the current multicentre prospective observational cohort study aims at reporting the long-term clinical outcomes of a novel uncemented knee system. We furthermore attempt to provide information on return to work and sports, utilizing validated outcome scales supplemented with performance based measurements as a proxy for physical performance (as recommended by Witjes et al.) [31]. This information can be used to inform patients of their chances to return to sports and work after TKA. Finally, we also seek to shed light on the role of pain behaviour and mental status in the long-term patient satisfaction after TKA.

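### The 10-year PROM associations are assigned to linear regression rather than to the mixed model already planned, so they may be attenuated and somewhat imprecise if loss to follow-up depends on outcome

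*Protocol article*

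**What the plan says.** The Statistical analysis section gives the same PROMs two methods in adjacent sentences. For the course over time: "Mixed model analysis for repeated measures will be used for assessment of change in PROMs scores during follow-up". For associations: "Multivariate linear regression analysis will be used to assess the association of radiolucent lines, implant alignment and preoperative psychologic scores", where the outcome is given as "with PROMs after 1, 5 and 10 years after index surgery".

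PROMs are available repeatedly: "Patients are asked to complete questionnaires before surgery and at every follow-up visit", which Table 1 sets at 6 months and 1, 5 and 10 years.

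The sample size paragraph in the same section inflates the calculated number for drop-out and "death within 10 years into account (approximately 20–25%), we are aiming for inclusion of" 900 knees.

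On non-return, the Discussion says: "Due to the highly successful nature of TKA, patients may not be willing to return for a clinical visit 10 years after surgery". It names the large number of outcome measures as another deterrent and then offers a possible mitigation: "Digital options for collection of the primary outcome measures (revision rate, complication rate and PROMs) can provide useful in this aspect".

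**The concern.** The method that can use incomplete follow-up is given to the question of change over time. The one that in its ordinary form cannot is given to the association question, which includes secondary objective 2: the long-term influence of preoperative psychological factors on satisfaction. The Background presents the long horizon as what is new, because most earlier studies stop at 1 year and one reaches 5.

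Ordinary linear regression of a 10-year score needs that score. A patient with PROMs at 6 months, 1 year and 5 years but none at 10 years contributes nothing to the 10-year coefficient. This is harmless for bias if loss is random or depends only on predictors in the model. If loss depends on how well the knee is doing, given those predictors, the coefficient is pulled towards zero. The Discussion raises that possibility itself.

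**Working it through.** **The plan's own figures.** The stated sample size reproduces as a one-sided, single-arm non-inferiority calculation:

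n = p(1 − p) × [(z₀.₉₅ + z₀.₉₀)/margin]² = 0.981 × 0.019 × [(1.645 + 1.282)/0.015]² ≈ 709.4, against 709 stated.

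Going from 709 to 900 implies attrition of 1 − 709/900 = 21.2%, inside the stated 20–25%. The allowance therefore belongs to the survivorship calculation, is counted in knees, covers 10 years and includes deaths. The article gives no separate PROM-missingness rate, no 5-year figure, and no sample size or precision for the PROM regressions.

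**Precision of a complete-case regression.** If the 20–25% carried over to 10-year PROMs (an assumption), 720 to 675 of 900 would have the score. The standard error relative to full data would be √(900/720) = 1.12 to √(900/675) = 1.15.

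**Bias.** The documents give no slope, within-patient correlation or loss mechanism, so these are assumed:
- 900 patients and 1,000 replicates per scenario;
- standardised slope −0.30 of the PROM on a preoperative score;
- four postoperative visits with within-patient correlation 0.3, 0.5 or 0.7;
- the 10-year value missing in 20% or 25% by a logistic model in which better scores are more often missing, with earlier visits complete.

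Two 10-year slopes are compared: least squares in patients with a 10-year score, and a likelihood-based repeated-measures estimate that also uses the earlier PROMs. The loss strengths of 0.7 and 1.5 log-odds per SD are odds ratios of e^0.7 = 2.0 and e^1.5 = 4.5. Ranges run over correlation and loss rate.

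| 10-year loss depends on | Complete-case attenuation | Repeated-measures attenuation |
|---|---|---|
| nothing, or the preoperative score only | about 0 (within 1.1%) | about 0 (within 1.0%) |
| 5-year PROM, 0.7 per SD | 1.6–4.6% | about 0 (within 0.6%) |
| 5-year PROM, 1.5 per SD | 5.1–13.7% | about 0 (within 0.5%) |
| unseen 10-year PROM, 0.7 per SD | 5.5–7.0% | 2.3–5.3% |
| unseen 10-year PROM, 1.5 per SD | 17.2–19.6% | 8.3–16.0% |

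The 1.1% deviation in the first row is simulation noise: the full-data slope in the same replicates deviates equally.

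The ratio of complete-case to repeated-measures standard error lies between 1.001 and 1.107.

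When loss follows the 5-year PROM, the attenuation in standard errors runs from 0.016 × 0.30/0.0340 = 0.14 to 0.137 × 0.30/0.0358 = 1.15.

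**A second set of assumptions.** Here loss depends on the 1-year score, half of those lost also miss 5 years, the correlation is 0.65, the residual SD is 8, the true effect is −2.5 points per SD, and there are 150 replicates.
- At an odds ratio of 2.7 per SD, complete cases give −2.33 (20% lost) and −2.30 (25% lost). That is (2.50 − 2.33)/2.50 = 6.8% and (2.50 − 2.30)/2.50 = 8.0% attenuation. Repeated measures give −2.50 and −2.49, with standard errors 4–6% smaller.
- At an odds ratio of 1.6, complete cases give −2.46 and −2.40, against −2.52 and −2.46. The standard error is about 8/√720 = 0.30, so Monte Carlo error is about 0.30/√150 = 0.024. The shortfall at 20% loss is not clearly more than noise.

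**The case against.** The strongest case against is that the article describes no complete-case analysis. A reader might infer that separate models are fitted and that patients without a visit are dropped. Neither is stated. Linear regression can be combined with multiple imputation, and an article commonly leaves that to a full protocol or SAP. This stands: missing detail on imputation is not the point. What remains is that the article assigns the association question to one of two methods it names, and the other uses the same data better.

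A reader might also infer that the plan expects good results to keep patients away, and so that missingness depends on outcome. The Discussion says only that this may happen, about a clinical visit and about the operation in general. Its other deterrent, the number of measures, need not relate to outcome, and digital PROM collection requires no visit. That weakens the mechanism without removing it, since digital collection is worded as a possibility.

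Third, 20–25% is not a PROM-missingness rate and says nothing about 5 years. Patients may be up to 90 at entry, so part of it is death, and a patient who has died has no 10-year score to recover. Treating the whole allowance as outcome-driven loss, as the simulations do, tends to overstate the bias.

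Fourth, the mixed model is no full cure, as the last two rows of the table show. The simulations also use a normally distributed score and a preoperative predictor, so they represent neither a numeric satisfaction rating nor the radiographic predictors. All of this stands and limits the point.

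Finally, visit-specific regression is a standard analysis for a secondary objective in a study that calls its statistics mainly descriptive. That makes this an improvement worth making rather than an error that invalidates the plan.

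**Conclusion.** The point holds as a choice of the weaker of two methods already in the plan. The 10-year associations may be attenuated; the documents do not support saying that they are. If loss follows earlier PROMs, the attenuation is about 2–14% and a repeated-measures model removes it. If loss follows the unseen 10-year score, it is about 6–20%, and 2–16% remains in the repeated-measures model. If loss is random or explained by modelled predictors, there is no bias and only a modest gain in precision (0–11% in standard error). All sizes rest on the assumed slope, correlations, loss mechanism and loss rate, and on treating 900 knees as 900 patients. Nothing here quantifies the 5-year regression.

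The case is clearest for the preoperative psychological scores, which are measured before any loss. It is weaker for radiolucent lines, read at follow-up visits, and for postoperative alignment, read at 1 year, because a missed visit also loses the predictor. The change should be made because it costs almost nothing and serves a stated objective.

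**What to change.** In the Statistical analysis section:

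1. For the preoperative psychological scores, estimate the 1-, 5- and 10-year associations as contrasts from the planned mixed model, with visit, predictor and predictor-by-visit terms.
2. Keep the visit-specific linear regression as a complete-case sensitivity analysis.
3. Add a sensitivity analysis for drop-out that depends on the unseen 10-year score, for example by shifting the assumed scores of those lost over a stated range.
4. Word the 10-year result as describing PROMs among patients alive, and count deaths apart from other loss. A mixed model treats a death like any other missing score, so this reading needs to be explicit.
5. For radiolucent lines and postoperative alignment, use only PROMs at or after the radiographic reading, and state that a missed radiograph loses the predictor as well.

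The cost is wording and slightly more modelling; every PROM involved is already scheduled. The downside is that the main estimate assumes loss is explained by observed scores and model predictors. That is weaker than what the complete-case regression needs, but it is still an assumption, which is why item 3 belongs in the plan.

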Besides surgical performance, patient characteristics and expectation management [5], several knee systems have been developed in an attempt to improve functional outcomes. One of these models is the uncemented Attune knee system (DePuy, Warsaw, Indiana, USA), first implanted in October 2016. One of the landmark features is a gradually reducing radius in the geometry of the femoral component, more closely mimicking the anatomical patellofemoral joint and facilitating more natural femoral rollback during flexion [6–8]. Its predecessor (Low Contact Stress, DePuy, Warsaw, Indiana, USA) had excellent results [9], but it is still unclear whether the newer, more costly, Attune outperforms it. Comparisons of the cemented Attune with previous knee systems show promising results in terms of patellofemoral outcomes [10–13], but fail to demonstrate definitive superiority in terms of all patient reported outcomes [10, 11, 14–19]. An important note is that all cited studies compare posterior stabilized implants, which are significantly different with regards to patellofemoral kinematics compared to cruciate retaining designs [20]. Clinical superiority of the Attune tends to abate with longer follow-up, implicating a possible advantage in short-term recovery and return to activities. There is no follow-up study reporting the results of the uncemented Attune. Moreover, all previously cited studies report better patellofemoral outcomes with patellar resurfacing, making it still unclear whether the implicated superior design changes of the femoral component hold ground without patellar resurfacing. Due to the significant differences in costs, the proposed superiority needs more scientific scrutiny to justify the higher implant price.

The primary objective of the current multicentre prospective cohort study is to report survivorship, complications, radiographic outcomes (i.e. alignment and radiolucent lines) and patient reported outcome measures associated with the uncemented Attune mobile bearing (“rotating platform”) cruciate retaining knee system without patellar resurfacing. Secondary objectives are (1) assess return to activities (work and sports) after TKA and (2) analyse preoperative psychologic factors and their influence on patient satisfaction following TKA.

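### The regressions of 1-, 5- and 10-year PROMs on preoperative psychological scores do not name the preoperative PROM, so their coefficients can partly reflect starting knee status

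*Protocol article*

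**What the plan says.** In the protocol article, Statistical analysis, the regression sentence sets the type of model (linear), the outcome (follow-up PROMs) and the factors of interest: radiographic findings and "preoperative psychologic scores (PSEQ, PCS and PHQ-2) with PROMs after 1, 5 and 10 years after index surgery". The outcome is a level at each time point, not a change from baseline. No adjustment covariate of any kind is named.

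The baseline value is available. Under Main outcomes: "Patients are asked to complete questionnaires before surgery and at every follow-up visit". Table 1 also marks PROMs as collected preoperatively.

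The same section has a separate analysis of change: "Mixed model analysis for repeated measures will be used for assessment of change in PROMs scores during follow-up". The psychological scores are not said to enter it.

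The secondary objective in the Background is to "analyse preoperative psychologic factors and their influence on patient satisfaction following TKA". The Abstract speaks of a long-term effect, and the Discussion of long-term impact and of possible interventions on pain beliefs before surgery.

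**The concern.** The psychological scores and the preoperative PROMs are measured at the same time in patients with a painful knee. By the article's own description (Secondary outcome – psychological factors), the PSEQ "asks patients to take their pain into account when rating their self-efficacy beliefs", and the PCS concerns catastrophic thinking about pain. The OKS, the AKPS and the pain ratings measure that same pain and the function it limits. A correlation between the two sets is therefore plausible. So is a relation between a patient's preoperative PROM and the later value of the same PROM.

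If both relations exist and the baseline PROM is left out, the psychological coefficient picks up part of the difference in starting knee status. The results are meant to inform whether changing pain beliefs before surgery could help. An association that only reflects a worse knee at baseline would not support that idea, and the unadjusted regression cannot tell the two apart.

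**Working it through.** **1. The plan's own figure.** The only computed figure is the sample size for 10-year survivorship. With p = 0.981, margin 0.015, one-sided α = 0.05 and power 0.90:

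n = p(1 − p)(z₀.₉₅ + z₀.₉₀)² / margin² = 0.981 × 0.019 × (1.645 + 1.282)² / 0.015² = 709.4.

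This reproduces the stated 709. The present point does not depend on it. It serves below only as a plausible number of knees with long-term data; the inclusion target is 900.

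**2. What the text names.**

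| Item | In the regression sentence? | Collected before surgery? |
|---|---|---|
| Preoperative PSEQ, PCS, PHQ-2 | yes | yes |
| Alignment | yes | yes, and at 1 year |
| Radiolucent lines | yes | no (from 6 months) |
| Preoperative value of the PROM | no | yes |

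**3. Size of the shift.** Use standardised variables and one psychological score at a time. Let r be the correlation of the score with the preoperative PROM. Let b be the effect of the preoperative PROM on the later PROM, given the score. Suppose the direct psychological effect is zero. Omitting the baseline then gives an expected coefficient of r × b in place of 0.

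The documents give neither r nor b. The values below are assumptions, shown as absolute sizes because the sign depends on how each scale is scored.

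**4. Chance of a significant result.** SE = √[(1 − (rb)²)/(n − 2)]. The two-sided 5% rejection probability is Φ(rb/SE − 1.96) + Φ(−rb/SE − 1.96).

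| r | b | r × b | n = 709 | n = 900 |
|---|---|---|---|---|
| 0.2 | 0.2 | 0.04 | 19% | 22% |
| 0.3 | 0.3 | 0.09 | 67% | 77% |
| 0.4 | 0.4 | 0.16 | 99% | nearly 100% |
| 0.5 | 0.5 | 0.25 | about 100% | about 100% |

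First row in full: SE = √[(1 − 0.0016)/707] = 0.0376 and 0.04/0.0376 = 1.06, which gives 19%. With the baseline in the model, the expected coefficient is 0 and the rejection rate 5%. If r or b is zero, there is no bias.

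**5. Precision.** Under the same assumptions, the SE of the psychological coefficient is proportional to √(1 − (rb)²) without the baseline and to √[(1 − b²)/(1 − r²)] with it.

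- r = 0.3, b = 0.5: √(0.75/0.91) / √(1 − 0.0225) = 0.908/0.989 = 0.918, so 8% smaller after adjustment.
- r = 0.5, b = 0.3: √(0.91/0.75) / √(1 − 0.0225) = 1.102/0.989 = 1.114, so 11% larger after adjustment.

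Over r and b from 0.3 to 0.5, adjustment can therefore make this SE smaller or larger. The case for adjustment is about bias and interpretation, not precision.

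**The case against.** The strongest reply is that silence is not exclusion. The sentence lists the exposures whose association is sought, and no model in the section has adjustment covariates such as age, sex or centre. The Cox model is described in the same way. A condensed article commonly leaves covariates to the full protocol or SAP. This stands in part: a reader might infer that the plan rules out baseline adjustment, or that a worse starting knee is certain to be reported as a psychological effect, and the text supports neither. What remains is that the article describes the outcome and explanatory variables of this analysis, and following that description gives coefficients mixed with baseline status.

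Second, adjustment is not automatically right. Preoperative PROMs are self-reported, and psychological state may shape them. In that case r × b is a real indirect effect, and adjustment removes it. The aim is also partly predictive: the Background asks whether catastrophising remains a predictor of dissatisfaction, and an unadjusted association suits that question. This stands, and is the reason to report both models rather than replace one with the other.

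Third, satisfaction with the TKA, the outcome in the objective, has no meaningful preoperative value, so the same-PROM adjustment is impossible there. This also stands. Preoperative OKS and pain can represent starting knee status, but they are substitutes.

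Fourth, the size is assumed, a zero direct effect is imposed, and one score is considered where the plan names three. All true; the figures illustrate and do not estimate.

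A reader might also infer that leaving out the baseline widens every confidence interval. Step 5 of the working shows that this does not hold for the psychological coefficients.

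**Conclusion.** The point holds in a limited form. The planned regressions of follow-up PROM levels do not name the preoperative PROM, although it is collected, and as written their psychological coefficients can partly reflect starting pain or function. With no direct effect and with r and b each assumed to be 0.2 to 0.5, the spurious standardised coefficient is 0.04 to 0.25. At 709 knees it would be significant in 19% to about 100% of studies. The direction of the argument is secure whenever both relations are non-zero; its size cannot be fixed from the documents.

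The unadjusted model is not wrong in itself. It answers a question about total or predictive association. It does not answer whether psychological factors matter beyond the state of the knee before surgery, and the objectives and Discussion use wording that invites that reading.

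**What to change.** In Statistical analysis, add the preoperative value of the same PROM as a covariate in each regression of 1-, 5- and 10-year PROMs. For the satisfaction NRS, use preoperative OKS and preoperative NRS pain.

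Report the psychological coefficients with and without this adjustment, and state the meaning of each in advance. The unadjusted coefficient is the total or predictive association; the adjusted one is the association beyond starting knee status. Base any statement that psychological factors influence outcome independently of baseline knee status on the adjusted model.

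The cost is a few sentences of wording and one extra set of coefficients, with no new data. The downside is that the adjusted model removes any part of a psychological effect that acts through preoperative pain. Reporting both models covers this. Fixing the wording before the follow-up data are analysed also prevents a choice between the models after the results are seen.
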